### Adverse Events (AEs)

The population targeted by the trial will experience a substantial degree of disease severity due to septic shock. Accordingly, consistent with best practice in ICU trials (25), we will capture major pre-defined AEs such as death, cardiopulmonary arrest, ECMO and amputations in study patients even if they are part of the natural history of the primary disease process. Any AE considered to be potentially causally related to the study intervention or which is of concern in the investigator's judgement will be reported. Specific AEs related to the intervention include, limb ischemia, extravasation injury, hypertension, arrhythmia other than sinus bradycardia or tachycardia, hyperglycaemia, abdominal compartment syndrome, pulmonary oedema and confirmed hospital-acquired infection.

Screening for adverse events will occur up until day 28, or until the time of patient discharge from hospital, whichever occurs earlier. An independent *Data and Safety Monitoring Board (DSMB)* consisting of one independent statistician, ICU specialist and emergency specialist each, who have no other involvement in the study, and who are not involved in study conduct, will review the progress and safety of the trial at regular intervals. No interim analysis for efficacy are planned.

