#### Early Inotropes

Patients in the intervention arm will receive an infusion of intravenous adrenaline immediately after randomisation, i. e. after the initial fluid bolus of 20 mL/kg (1,000 mL fluid bolus in patients >50 kg). Adrenaline will be initiated at 0.05 to 0.1 (up to 0.3) microgram/kg/min as per institutional guidelines. For the administration, adrenaline 1 mg will be diluted in 49 mls of 5% Dextrose. The dilution is used to hasten drug delivery and response to drug rate changes, to reduce risks with extravasation, and to facilitate peripheral application. Drug delivery will occur through dose error reduction software for infusion devices to ensure safe delivery of applied standardised drug concentrations. In emergency situations, adrenaline can be given through a peripheral intravenous, intraosseous, or central venous access line. Once started, adrenaline should be delivered for 60 min at a dose titrated to age-based physiological targets in patients who show signs of stability before weaning the drug. Patients who are successfully weaned off adrenaline within <4 h can in principle be admitted to the ward, yet should be reviewed by PICU staff within 4–6 h after transfer from ED. In patients deteriorating despite adrenaline infusion, the dose rate should be increased and admission to PICU with appropriate monitoring sought as per local practice.

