#### Standard Care

In the standard arm, patients will receive standard care as per site specific protocols based on international guidelines (11, 13). Specifically, patients in the standard arm will receive 40–60 mL/kg of fluid bolus therapy prior to initiating inotropes, thus, 20–40 mL/kg bolus fluid *after* randomisation (in addition to the 20 mL/kg bolus fluid, or 1,000 mL fluid bolus in patients >50 kg, which has to be administered to meet enrolment criteria). Further fluid and inotrope decisions in the standard care arm are at the discretion of the treating physician. The standard care is aligned with education provided at the study sites through the Paediatric Sepsis Pathway project (Queensland Sepsis collaborative) since 2018, which advocates for the administration of sepsis resuscitation bundles as per the Surviving Sepsis Campaign.

Patients who improve in <4 h can in principle be admitted to the ward as per local practice. In patients deteriorating despite 40–60 ml/kg fluid boluses, inotropes should be commenced, and the dose rate should be increased until stabilisation occurs. Admission to PICU with appropriate monitoring should be sought as per local practice.

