### Study Outcomes

This pilot study includes feasibility outcomes, as well as clinical primary and secondary outcome measures, and proxy measures of intervention efficacy (Table 2). The *feasibility outcomes* include consent rates; compliance measures such as time to inotropes, amount of fluid delivered during the first 24 h; and protocol violations. The *clinical primary outcome* is survival free of organ dysfunction, censored at 28 days. Organ dysfunction will be assessed by pediatric Sequential Organ Failure Assessment (pSOFA) scores (23). Patients dying within 28 days of presentation will be considered as zero days to correct for the competing effect of mortality on duration of organ dysfunction. Patients discharged alive from PICU to the ward or home not requiring ongoing respiratory or renal support, and not under palliative care will be assumed to have no organ dysfunction after PICU discharge. *Secondary clinical outcomes* include PICU free survival, survival free of inotrope support and free of multi-organ dysfunction (defined as >1 organ with a pSOFA score >0), mortality, and PICU and hospital length of stay. In addition, we will obtain Pediatric Overall Performance Category and Functional Status Score at 28 days (24). Long-term follow-up will be performed at 6 months post randomisation using assessment of quality of life using neurodevelopment, quality of life and functional status, and will be reported separately. *Proxy measures of intervention efficacy* include the proportion of study participants with a blood lactate level <2 mmol/L at 6, 12 and 24 h, time to reversal of tachycardia [defined by the upper age-specific thresholds for Systemic Inflammatory Response Syndrome (22)], and time to reversal of shock (defined as cessation of inotropes for at least 4 h). Ancillary studies assessing sepsis-related costs are pre-planned but will be reported separately.

**Table 2 T2:** Outcomes assessed.

**Outcome**	**Criterium**	**Definition**
Feasibility of the protocol	Compliance with study protocol	• Recruitment rates; proportion of eligible randomised, proportion of eligible consented using prospective consent and consent to continue. • Time to initiation of inotropes between the control and the early inotrope arm • Amount of fluid delivered (in mLs per kg) during the first 24 h between the control and the early inotrope arm • Protocol violations

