### Data Collection

Site visits for start up and ongoing education support are provided alongside a RESPOND ED specific resource booklet to assist in time-sensitive enrolment for clinicians and trial management. Demographic variables, severity at baseline, primary end points, secondary end points, proxy measures of intervention efficiency, feasibility measures, primary diagnoses, physiological parameters, diagnoses, therapeutic interventions and documentation of deaths and other serious adverse events will be prospectively recorded into a purpose-built REDCap online database (26), hosted by The University of Queensland (Table 3). All data will be collected by trained staff at each study site using a series of electronic case report forms (eCRFs) developed by the coordinating centre. Randomized patients will be followed up by study nurses until death or 28 days post-randomisation whichever occurs first, with a follow-up review performed 6 months after randomisation. Day-28 and 6-month follow-ups will occur by phone unless the patient is still in hospital. Details on long-term follow up will be published separately. Data collection will consider the following as inotropes or vasopressors: adrenaline, noradrenaline, vasopressin, milrinone, dopamine, dobutamine. The study protocol mandates the use of adrenaline as first line inotrope.

**Table 3 T3:** Study schedules to be captured in the study database.

**Study phase**	**Item**
Enrolment	• Screening & eligibility checks • Consent information • Baseline data including patient characteristics, treatment received, severity and physiology • Randomization
Interventions	• Time of and volume of fluid administered during first 24 h • Time of, type, and dose of inotropes administered
Early assessment	• Daily assessment of organ dysfunction using pediatric Sequential Organ Failure Assessment (pSOFA) • Organ support (respiratory and/or cardiovascular including extracorporeal membrane oxygenation, and renal support) • Laboratory markers of organ function and infection/inflammation
Late assessment	• Survival assessment at 28 days • Questionnaires by proxy on Functional Status Score and Pediatric Overall Performance Category at 28 days • Questionnaires by proxy on neurodevelopment, quality of life and functional status 6 months post enrolment

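### Active adverse-event screening ends at hospital discharge when that precedes day 28, so non-fatal serious events between discharge and day 28 are not actively sought and the window varies with length of stay, although a day-28 contact is already planned

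*Protocol article*

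**What the plan says.** All references are to the protocol article.

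- **Adverse Events (AEs), end of screening:** "Screening for adverse events will occur up until day 28, or until the time of patient discharge from hospital, whichever occurs earlier".
- **Same section, scope:** "we will capture major pre-defined AEs such as death, cardiopulmonary arrest, ECMO and amputations in study patients", even where they belong to the natural course of the disease. A second list covers events tied to the intervention: "Specific AEs related to the intervention include, limb ischemia, extravasation injury, hypertension, arrhythmia other than sinus bradycardia or tachycardia, hyperglycaemia", followed by abdominal compartment syndrome, pulmonary oedema and confirmed hospital-acquired infection. Any event thought causally related, or of concern to the investigator, is to be reported. No time limit is attached to that sentence.
- **Data Collection, follow-up:** "Randomized patients will be followed up by study nurses until death or 28 days post-randomisation whichever occurs first". The contact is specified: "Day-28 and 6-month follow-ups will occur by phone unless the patient is still in hospital". The day-28 items in Table 3 are survival and proxy questionnaires on function.
- **Study Outcomes:** the secondary outcomes include "mortality, and PICU and hospital length of stay".
- **Blinding and Analysis:** the trial is open label, and adverse events are presented descriptively.

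**The concern.** The screening rule ties the length of safety observation to discharge, which happens after randomisation and which treatment may affect. The trial acknowledges this possibility by comparing hospital stay between the arms. The main clinical outcome and mortality are judged over a fixed 28 days, whereas active safety screening can stop sooner.

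Two things follow. Serious non-fatal events between discharge and day 28 have no active route to detection. Cardiopulmonary arrest, ECMO and amputation are among the events the protocol commits to capturing, and limb ischaemia and extravasation injury can be recognised late. Also, if one arm goes home sooner, it is screened for less time, and raw event counts by arm do not share a denominator. At stake is the completeness of the safety description that a pilot passes on to the full trial.

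**Working it through.** **1. Setting the sections side by side.**

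| Item | Observation ends at | Depends on discharge? |
|---|---|---|
| Active AE screening | earlier of discharge and day 28 | yes |
| Nurse follow-up | earlier of death and day 28 | no |
| 28-day mortality | day 28 | no |
| Day-28 contact | day 28, by phone or in hospital | no |
| Reporting of events judged related or of concern | no limit stated | no, but unsolicited once screening has stopped |

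The gap is therefore specific: non-fatal events, after discharge, before day 28.

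**2. Inputs for the size.** The documents give no length of stay, no adverse-event rate and no event timing, so there is no figure of theirs to reproduce. Everything below is assumed: log-normal hospital stay with SD(log) 0.9, event timing independent of discharge, and the same true risk in both arms. Write S(t) for the probability of still being in hospital at day t.

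**3. Screened time.** Mean screened days = ∫₀²⁸ S(t) dt.

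| Median stay | Home before day 28 | Mean screened days | Share of 28 days |
|---|---|---|---|
| 6 days | 96% | 8.34 | 30% |
| 8 days | 92% | 10.55 | 38% |
| 12 days | 83% | 14.14 | 51% |

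**4. Constant daily hazard, medians 8 versus 6 days.** Ratio of screened time = 10.55 / 8.34 = 1.265, so about 26% more events are recorded in the arm with the longer stay although the true risk is equal. In children: with an assumed 28-day risk of 20% and 20 children per arm, the expected numbers recorded are about 1.6 versus 1.3. That is a difference of about a third of one child. A fixed window would give 20 × 0.20 = 4.0 in each arm.

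**5. Front-loaded events, same stays.** Let a share f of events fall evenly in days 0 to k and the rest evenly from k to 28. The share recorded is f·(1/k)·∫₀ᵏ S(t) dt + (1 − f)·(1/(28 − k))·∫ₖ²⁸ S(t) dt.

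| f | k (days) | Recorded, median 8 | Recorded, median 6 | Ratio |
|---|---|---|---|---|
| 0.9 | 1 | 0.933 | 0.922 | 1.01 |
| 0.8 | 1 | 0.869 | 0.850 | 1.02 |
| 0.9 | 3 | 0.891 | 0.852 | 1.05 |
| 0.8 | 3 | 0.826 | 0.782 | 1.06 |
| 0.9 | 5 | 0.823 | 0.759 | 1.08 |
| 0.8 | 5 | 0.761 | 0.695 | 1.09 |

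The distortion is 1–9%.

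**6. Equal stays.** The ratio is 1.00 under either timing, but events after discharge still go unrecorded. In the table above, the unrecorded share runs from about 7% (1 − 0.933) to about 30% (1 − 0.695). These shares are likely to be high, because children who are developing a complication tend to stay in hospital, whereas the model treats timing and discharge as independent.

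**The case against.** The case for the rule as written is substantial.

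- **Timing of the events.** Most of the listed intervention-related events are acute and belong to the hours or days of infusion and fluid boluses. A constant hazard over 28 days does not fit them. This stands, and it is why the 1–9% range is the more plausible one for the list as a whole.
- **Direction of stay.** Nothing in the documents says which arm goes home sooner, or that the arms differ. Both arms allow early ward care: "Patients who are successfully weaned off adrenaline within <4 h can in principle be admitted to the ward" in the intervention arm and "Patients who improve in <4 h can in principle be admitted to the ward as per local practice" in the standard arm. Ward admission is not hospital discharge, so neither provision ends screening. This stands.
- **Other routes.** Death is assessed at day 28 whatever the discharge date. Functional scores at day 28 may reflect a lasting loss such as an amputation, though not as a coded event. Related or concerning events remain reportable, and Data Collection provides for recording serious adverse events without naming a discharge cut-off. This stands in part: none of these is an active enquiry about non-fatal events after discharge, and unsolicited reporting in an open-label trial need not be even between arms.
- **Verifiability.** In-hospital events can be checked against source records, and the plan verifies reported adverse events in all randomised, consented patients. Parents cannot report hyperglycaemia or arrhythmia reliably. This stands, and it limits what the day-28 enquiry should cover.
- **Consequence.** Adverse events are descriptive in 40 children, so no test or decision rule is biased. This also stands.

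A reader might infer from Table 3 that the day-28 call contains no safety question. The documents do not support that: this is a condensed article, and the full protocol and case report forms are not shown. The point rests on the stated screening rule, not on what the table leaves out.

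**Conclusion.** The point holds in a limited form. As stated, the rule ends active screening at discharge, lets the window vary with a compared outcome, and leaves non-fatal serious events between discharge and day 28 unsought despite a planned contact at that day.

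A reader might go further and conclude that the comparison of adverse events between arms is biased by about a quarter, or that late deaths are missed. Neither is supported. The 26% needs both an assumed difference in stay (medians 8 versus 6 days) and a constant daily hazard. With events concentrated in the first 1 to 5 days it falls to 1–9%, and with equal stays it vanishes. Deaths are captured to day 28. With 20 children per arm, even the constant-hazard case amounts to about a third of one child.

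The firmer consequence is incomplete capture of a few serious late events, which does not depend on the arms differing in stay. In an arm of 20, one missed event shifts the observed proportion by 1/20 = 5 percentage points. This is an inexpensive improvement to safety ascertainment, not a flaw that undermines the trial.

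**What to change.** Split the adverse-event window by type of event.

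1. **Common 28-day window from randomisation** for the pre-defined major events (death, cardiopulmonary arrest, ECMO, amputation), for any readmission, and for late-recognised limb or skin injury. Ask about these at the existing day-28 contact for children who are alive, consented and reachable. Verify each positive answer from hospital records, and report how many children completed the enquiry in each arm.
2. **In-hospital window** for acute monitored events such as hypertension, arrhythmia, hyperglycaemia and confirmed hospital-acquired infection. Report these by arm with patient-days at risk, so that a difference in stay is visible beside the counts.
3. **One sentence in the Adverse Events section** stating which events follow which window, consistent with the follow-up described under Data Collection. If the full protocol or case report form already has a day-28 safety enquiry, the sentence should say so.

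The cost is a few questions on a contact already scheduled, a small case report form change and a protocol line. No extra visit and no change in sample size are needed. The downside is reliance on parent recall, with parents aware of the allocation, and a record check for each positive answer.

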### Data Collection

Site visits for start up and ongoing education support are provided alongside a RESPOND ED specific resource booklet to assist in time-sensitive enrolment for clinicians and trial management. Demographic variables, severity at baseline, primary end points, secondary end points, proxy measures of intervention efficiency, feasibility measures, primary diagnoses, physiological parameters, diagnoses, therapeutic interventions and documentation of deaths and other serious adverse events will be prospectively recorded into a purpose-built REDCap online database (26), hosted by The University of Queensland (Table 3). All data will be collected by trained staff at each study site using a series of electronic case report forms (eCRFs) developed by the coordinating centre. Randomized patients will be followed up by study nurses until death or 28 days post-randomisation whichever occurs first, with a follow-up review performed 6 months after randomisation. Day-28 and 6-month follow-ups will occur by phone unless the patient is still in hospital. Details on long-term follow up will be published separately. Data collection will consider the following as inotropes or vasopressors: adrenaline, noradrenaline, vasopressin, milrinone, dopamine, dobutamine. The study protocol mandates the use of adrenaline as first line inotrope.

**Table 3 T3:** Study schedules to be captured in the study database.

**Study phase**	**Item**
Enrolment	• Screening & eligibility checks • Consent information • Baseline data including patient characteristics, treatment received, severity and physiology • Randomization
Interventions	• Time of and volume of fluid administered during first 24 h • Time of, type, and dose of inotropes administered
Early assessment	• Daily assessment of organ dysfunction using pediatric Sequential Organ Failure Assessment (pSOFA) • Organ support (respiratory and/or cardiovascular including extracorporeal membrane oxygenation, and renal support) • Laboratory markers of organ function and infection/inflammation
Late assessment	• Survival assessment at 28 days • Questionnaires by proxy on Functional Status Score and Pediatric Overall Performance Category at 28 days • Questionnaires by proxy on neurodevelopment, quality of life and functional status 6 months post enrolment

Physiological parameters and study treatment (fluids and inotropes) will be collected upon randomisation, then at 20-min intervals during the first 4 h, and at six, 12 and 24 h subsequently. The total fluid given will be captured at one, four, 12 and 24 h. Organ dysfunction and organ support will be collected upon randomisation, by 24 h and thereafter daily whilst treated in PICU for a maximum of 28 days. In addition, we will capture initiation of antibiotic therapy, intravenous steroids, duration of inotrope and/or vasopressors and respiratory support, PICU discharge, hospital discharge, death and cause of death. Protocol deviations and reasons for such will be recorded.

### Biobanking

If parents/caregivers provide consent, samples containing 1–2 mL of EDTA blood, 2.5 mL of PAXgene blood RNA, and 1–2 mL of serum will obtained at enrolment for future studies of markers of sepsis, sepsis susceptibility, and sepsis severity. Biobanking does not affect the study conduct nor randomisation. The samples will be processed, stored and assessed in batch according to standard operating procedures.

### Data Quality and Monitoring

Extensive study education is being provided to ensure medical and nursing clinicians at participating sites are well-informed about the trial. In addition, a contact phone number of study staff being available 24/7 is provided with the study booklet, flyers, and posters at the sites to enable rapid contact with research staff once a child is considered for the study. The site principal investigator will be responsible for local oversight of the study including safety reporting, ensuring that the study is conducted according to the protocol, and ensuring data integrity. Monitoring will be performed in 100% of randomized and consented patients using primary source data verification to verify randomisation allocation and commencement of intervention and consent, treatment of intravenous bolus and inotropes during the first 24 h of enrolment, organ support intervention within 28 days, PICU admission and discharge time, survival status at ED, PICU and hospital discharge, reported protocol deviations and adverse events. In 10% of randomly selected patients, we will monitor inclusion and exclusion criteria for ineligible patients, and for randomized and consented patients, baseline data, first 24 h data, demographic data, daily organ dysfunction data, ED and hospital discharge data to ensure fidelity and accuracy of obtained data. A site initiation teleconference will be conducted before site activation to ensure consistency in procedures, followed by regular videoconferences between research staff at the study sites. A data dictionary and study booklet are provided prior to study sites going live.

### Statistical Analysis Plan

#### Sample Size

A recruitment period of 24 months is the projected time to achieve the required sample size of 40 participants. The size of the pilot (*N* = 40) was chosen to reflect about 10% of a full trial to yield sufficient data in relation to feasibility. We estimate that ~50 children each year are treated for septic shock in the main participating ED. Assuming that 30–40% of children will meet exclusion criteria, and anticipating 50% enrolment rates, completion within 24 months is projected to be feasible.

